### Study design

The design uses a cluster randomized trial with a phased rollout to evaluate the differential effectiveness of the Core and Enhanced conditions in 36 sites (18 matched pairs—see below) in 7 states. The design features randomization to one of two conditions, randomization to one of three cohorts (with start times spaced 2 months apart), the inclusion of a baseline period in both experimental conditions, and data collection at regular intervals (enabling time series analyses; see Fig. 3). In addition to comparing the two implementation conditions, it also allows sites to serve as their own controls by using an interrupted time series design with the baseline period as an existing practice control. This design enables three time-series comparisons: (1) Baseline (“activities as usual”) versus Core, (2) Baseline versus Enhanced, and (3) Core versus Enhanced.

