### Measurement

A multilevel approach to measurement is necessary for our understanding of change processes within complex service systems [36, 66]. Youth interact with JJ agency staff who work within a larger organization; in turn, the organization operates within a system that includes BH providers, oversight agencies, and funders. The proposed measurement plan assesses information from these levels.

The design employs three data collection periods: baseline (6 months; generally corresponding to EPIS’ Exploration and Preparation phases), experiment (12 months; corresponding to EPIS’ Implementation phase), and post-experiment (6 months; corresponding to EPIS Sustainment phase). Figure 4 includes a timeline depicting all intervention components (top portion) and data collection (bottom portion) for sites in wave 1. During baseline, RCs initiate collection of de-identified youth records data related to the Cascade dating back to October 1, 2014, administer agency surveys, conduct a local needs assessment (systems mapping exercise and group interview with interagency workgroup members), and administer leadership and line staff surveys at participating agencies. Leadership and line staff complete follow-up surveys during months 2 and 12 of the experiment period and again at month 6 of the post-experiment period. A representative from each site reports progress toward site-selected goals (i.e., implementation activities) during a monthly site check-in phone call. In the Enhanced condition, local change team members complete implementation process surveys during the experiment period. The 6-month post-experiment period consists only of data collection, including youth record extraction, agency and staff surveys, group interview (to determine whether sites sustain new practices), and monthly site check-in calls. Data collection components are summarized in Table 2.

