### Hypotheses

Table 3 summarizes the primary hypotheses corresponding to the research questions above. H1 and H2 focus on retention in the Cascade: H1 compares both experimental conditions to their respective baseline period, whereas H2 compares the differential effectiveness of Core versus Enhanced sites. Table 3 shows the working definition and formula for the rates of each step within the Cascade (see Fig. 1), designed to map onto existing and widely used performance metrics systems (Center for Substance Abuse Treatment adolescent treatment branch and National Outcome Monitoring System; the Network for the Improvement of Addiction Treatment (NIATx); the National Quality Forum; the Office of National Coordinator of Healthcare Reform; and Washington Circle Group). The rates shown are proportions of youth receiving the service within each site, divided by the number in the earlier step, with dashed lines highlighting changes in the denominator.

**Table 3 Tab3:** JJ-TRIALS research questions and hypotheses

Primary research question	Corresponding hypotheses
1. Does the Core and/or Enhanced intervention reduce unmet need by increasing service cascade retention related to screening, assessment, treatment initiation, engagement and continuing care?	*H1:* Compared to baseline period, the percentage of *youth retained in the service cascade* will increase during the experiment period (in terms of % screened, % assessed, % in need, % referred, % initiated, % engaged, and % continuing care).
2. Does the addition of the Enhanced intervention components further increase the percentage of youth retained in the service cascade relative to the Core components?	*H2:* Compared to the Core intervention sites, the Enhanced Intervention sites will have greater improvements (relative to baseline) during the experiment period in their percentage of *youth retained in the service cascade* (in terms of % screened, % assessed, % in need, % referred, % initiated, % engaged, and % continuing care).
3. Does the addition of the Enhanced intervention components improve service quality relative to Core sites?	*H3:* Compared to the Core intervention sites, the Enhanced intervention sites will have greater improvements (relative to baseline) during the experiment period in service quality in terms of:
	a) *timing* (e.g., shortened length of time between arrest and screen),
	b) *content* (e.g., increased use of EBP to screen), or

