	c) *procedure* (e.g., increased number of staff trained on using an EBP screener).
	(NOTE: H3b & H3c are largely descriptive and exploratory.)
4. Do staff perceptions of the value of best practices increase over time, and are increases more pronounced in enhanced sites? [staff within sites]	*H4:*
	*a)* Relative to Staff at the Core sites, staff at Enhanced sites will show a greater increase between baseline and end of experimental period in the perceived “value” and reported use of *evidence-based substance use treatment services* along the Cascade.
	b) Staff in both Core and Enhanced sites will show an increase between baseline and end of core support period in the perceived “value” of *HIV/STI prevention, testing, and treatment services*.
	c) Staff in both Core and Enhanced sites will show an increase between baseline and end of core support period in the perceived “value” of *evidence-based substance use prevention services*.

Latent Growth Curve Modeling (LGCM) will be used to test H1 and H2 using MPLUS [68]. A significant change in the slope between the baseline and experimental time periods (H1) or between Core and Enhanced conditions (H2) would suggest that the intervention affected the growth curve. This analysis will be repeated for each targeted outcome measure in the Cascade. To the extent that there are site differences, data can be analyzed within sites, using non-parametric simplified time series (STS) analysis [69, 70]. MPLUS will also allow examination of time-varying covariates to determine whether early implementation activities have significant effects on later time points.

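### H1 and H2 predict a higher percentage of youth retained, but the only stated test is a change in growth-curve slope, which can miss a prompt, sustained gain

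*Protocol article*

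**What the plan says.** In the Hypotheses section, Table 3 words H1 as a percentage retained that "will increase during the experiment period (in terms of % screened, % assessed, % in need, % referred, % initiated, % engaged, and % continuing care"), compared with the baseline period. H2 says that "the Enhanced Intervention sites will have greater improvements (relative to baseline) during the experiment period in their percentage of" youth retained, compared with Core sites. Both are directional and both refer back to baseline.

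The text after Table 3 gives the method: "Latent Growth Curve Modeling (LGCM) will be used to test H1 and H2 using MPLUS". The criterion follows: "A significant change in the slope between the baseline and experimental time periods (H1) or between Core and Enhanced conditions (H2"). The article takes such a result as a sign of an effect on the growth trajectory. The analysis is repeated for each Cascade outcome. A simplified time series analysis is mentioned as an option within sites, if sites differ.

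The Study design section describes sites as their own controls, "using an interrupted time series design with the baseline period as an existing practice control". The Measurement section sets the phases as "baseline (6 months; generally corresponding to EPIS’ Exploration and Preparation phases") and "experiment (12 months; corresponding to EPIS’ Implementation phase").

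**The concern.** A percentage that is higher in one period than in another is a statement about level. A slope change is a statement about how fast the percentage moves. The two agree if improvement is a steady climb. They part if a site adopts, say, a standard screener, its rate moves promptly to a higher value and then stays there: H1 is then true as written, yet the experiment-phase slope is flat. Each Cascade rate is a percentage, so a sustained gain must flatten at some point.

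At stake is the reading of the two main service-delivery hypotheses. A real improvement could fail the stated criterion, and under some model forms could give a slope change of the opposite sign. The criterion also leans on a baseline slope, which is estimated much less precisely than a baseline mean when the baseline is short.

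**Working it through.** **Inputs from the article.** Baseline 6 months and experiment 12 months (Measurement), taken as 13 and 26 bi-weekly periods. 18 sites per condition (Main trial). ICC .2, the upper value in Power. Records dating back to October 1, 2014 (Measurement). Wave 1 starting April 2015 (Main trial), with experiment activities from month 8 (Table 1).

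**The plan's own figures.** Power gives 36 × 60 = 2160 bi-weekly observations, which reproduces. The stated phases (6 + 12 + 6 months) give 13 + 26 + 13 = 52 periods, not 60, so the length of the series that enters the model is not settled. If records from October 2014 are used, wave 1 has about 13 months before November 2015, or about 28 pre-experiment periods; wave 3, starting four months later, has about 37. The power statement (effects of .25 to .35) does not say whether it concerns a mean or a slope, so it does not decide this point.

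**What a pure step does to the slope change.** Take a noise-free series that is 0 in baseline and +1 SD throughout 26 experiment periods, and fit it by least squares.

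- Separate level and slope in each phase: slope change is 0 for every baseline length. The whole effect sits in the level term (+1).
- Two slopes joined at the phase boundary, slope change expressed over 26 periods:

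| Baseline periods | Joined-curve slope change (SD) |
|---|---|
| 13 | -1.51 |
| 21 | -0.36 |
| 26 | 0.00 |
| 28 | +0.11 |
| 32 | +0.28 |
| 37 | +0.45 |

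The phase-mean difference is +1 in every row.

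**Gradual gains to +1 SD, slope change over 26 periods.**

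- Ramp over 6 months, then plateau: +1.00 (separate) and +0.62 (joined) with 13 baseline periods; +1.00 and +1.03 with 28.
- Ramp over 3 months, then plateau: +0.62 and -0.23 with 13; +0.62 and +0.68 with 28.
- Steady rise over 12 months: +1.00 under both forms.

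**Precision for the H2 contrast.** Assumed: total variance 1, residual variance .8, independent residuals, no between-site variation in response, two-sided 5% test, 80% power (multiplier 2.80). With nb baseline and ne experiment periods:

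- Mean change, variance per site = .8 × (1/nb + 1/ne).
- Slope change (separate phases), variance per site = .8 × [12/(nb(nb² − 1)) + 12/(ne(ne² − 1))].
- Standard error of the difference between conditions = √(2 × variance/18).

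*13 baseline periods.* Mean change: .8 × (1/13 + 1/26) = .0923; standard error .1013; detectable difference 2.80 × .1013 = .284 SD. Slope change: .8 × [12/(13 × 168) + 12/(26 × 675)] = .00494; standard error .0234; detectable divergence at the end of the experiment 2.80 × .0234 × 26 = 1.71 SD. For a steady rise the mean divergence is half of that, .85 SD, and .85/.284 = 3.0. The joined curve gives 1.48 SD at the end, mean .74, ratio 2.6.

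*28 baseline periods.* Mean change: .8 × (1/28 + 1/26) = .0593; detectable difference .227 SD. Slope change: .8 × [12/(28 × 783) + 12/(26 × 675)] = .000985; end divergence .76 SD, mean .38 SD; ratio .38/.227 = 1.7. The joined curve gives the same ratio.

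**Illustrative simulation.** It uses 13 + 26 periods, 5 youth per period and steps of +5 points (Core) and +15 points (Enhanced). Assumed, not in the article: a 40% baseline rate and between-site SDs of 12 points (level), 5 points (step) and 5 points per 26 periods (slope). The mean-change contrast was significant in the right direction in about 100% of runs for H1 and 87% for H2. Slope change with separate phases managed 2% and 3%. The joined curve managed 0% for both, with wrong-direction significance in 60% and 20% of runs. The joined-curve figures belong to the 13-period baseline.

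**The case against.** The strongest reply has four parts.

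1. **Baseline length.** Records go back to October 2014 and Power counts 60 periods per site, so 13 baseline periods may not be what is modelled. This stands. A reader might infer from the 13-period result that the test reverses the sign of a real gain. The documents do not support that as a general statement: it needs a joined curve with a baseline shorter than the experiment phase for a step at the boundary, and it has gone by 26 to 28 periods. The threefold precision loss likewise belongs to the short baseline.

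2. **Shape of response.** The article describes rapid-cycle testing, revised plans and 12 months of facilitation, and sites that adopt at different times average to a ramp. This also stands in part: an immediate step at all sites is the extreme case, and a ramp is partly picked up. But the hypotheses do not specify a shape, so the test should not depend on one.

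3. **H2.** The words can be read as a difference between conditions in one growth slope over both phases. A step then appears as a steeper slope, with 72% power in the simulation above. A reader might infer that the H2 test is shown to miss a step; that is not established. That reading does not rescue H1, because a single line has no slope change between phases, and H2 is itself worded relative to baseline.

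4. **Condensed article.** Level terms are details that a full plan may hold, and the article does not say that a level change would be ignored or an intervention declared ineffective. True, but the article does not leave the criterion open: it names slope, for hypotheses worded as level. The simplified time series is conditional, optional and within site, so it does not fill the gap.

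**Conclusion.** The point holds as a mismatch between hypothesis and test, clearest for H1. With phase-specific levels and slopes, a prompt and sustained gain gives zero slope change whatever the baseline length; this is algebra and needs no assumed rates. With a joined curve the answer for the same +1 SD gain runs from about -1.5 SD (13 baseline periods) through zero (26) to slightly positive (28 and more), so the conclusion would turn on which records are counted as baseline. It is not a universal sign reversal, and a steady rise is properly detected.

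The precision cost against a mean-change contrast is about 1.7-fold with 28 baseline periods and 3-fold with 13. Both figures assume independent residuals and no between-site variation in response. Sites choose different goals and practices, so such variation is likely, and the detectable differences quoted for either contrast are optimistic.

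**What to change.** State the primary H1 contrast as the model-based difference in percentage between the experiment and baseline periods, and the primary H2 contrast as the difference between conditions in that change. Estimate both from a segmented growth model with a level-change and a slope-change term, and report slope change as a secondary description. Say in the same place which records form the baseline series, since results from a joined curve depend on it.

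The cost is wording: the data and software stay the same. The downside is that the claim about the shape of growth becomes secondary.

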#### Randomization

The design features two stages of randomization: (a) to one of three start times as part of a phased rollout and (b) to the Core or Enhanced condition. The CC was responsible for all randomization procedures. For the first stage, RCs were used as strata and the six county sites within each were matched into pairs in terms of the number of youth (ages 10–19) in the county based on the 2010 census, the number of youth entering community supervision, the number of staff in community supervision, whether they used standardized screeners/assessments and evidence-based treatment. Each RC PI reviewed matches and ensured comparability prior to randomization. Within each RC, the three resulting pairs were then randomly assigned to one of three start times using a random number generator in Excel. This procedure was utilized to smooth out the logistical burden of implementation and to control for the influence of other exogenous factors [63, 64].

For the second stage of randomization, one site in each pair was randomly assigned to Core and the other to Enhanced. Given that there were only 18 pairs of sites, “optimal” randomization was used to find the most balanced pattern of assignment across each RC. This approach involved running 10,000 permutations of the possible assignments of sites within each pair to condition. For each of these, multivariate Hotelling’s *T*
^2^ was computed to assess the degree of balance on cohort and condition both within and across all RCs. The final randomization design was selected from a pool of the top 2 % of permutations balancing across all characteristics.

The study is also double-blinded such that neither the RC staff nor any county site staff are aware of their assignment until after both sites in a pair have completed the Core components. Once completed, the condition of both sites is revealed by the CC PI to RC PI and, subsequently, to sites. This design aspect is ideal in studies with multiple sites that have initial variability and require intensive researcher-driven activities such as training, monitoring, or coaching.

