H3a utilizes bi-weekly intake cohorts and tests whether percentages of youth meeting “timing targets” differ significantly between the 18 Enhanced and the 18 Core sites. Records data include dates to allow examination of time between various points in the Cascade (see Table 4). Trends can be examined over time using simplified time series analysis. H3b and H3c are considered exploratory, using data from agency surveys and needs assessment group interviews (measured twice: baseline and end of experiment; see Table 5). Survey content is derived from the JJ-TRIALS National Survey (developed by Chestnut Health Systems and administered in 2014). Group interviews (recorded and transcribed) generate descriptive detail on the entire Cascade, including system capacities, referral processes, the nature and use of screening instruments, the quality of available services, and features in the inner and outer contexts of agencies likely to influence service delivery.

**Table 4 Tab4:** Measures from de-identified records corresponding to the Behavioral Health Service Cascade

Step	Operational definition	Rate
a. JJ referrals	Total number of referrals to juvenile justice in time period with a disposition start date, less any youth already in treatment at that time	–
b. Screened	Subset of JJ referrals (a) with a screening date	b/a
c. Clinical assessment	Subset of JJ referrals (a) with a full clinical assessment (includes if follow-up to screening or other clinical assessment)	c/a
d. Need identified	Subset of JJ referrals (a) with a need for substance use treatment based on screener, urinalysis, clinical assessment, or other sources of information	d/a
e. JJ Referrals to treatment	Subset of those in need (d), referred by the juvenile justice system to substance use treatment	e/d
f. Initiated treatment	Subset of those referred to treatment (e) who have treatment start date	f/e
g. Engaged in treatment	Subset of those who initiate treatment (f) who stay in treatment for at least 6 weeks (based on treatment discharge minus treatment start date)	g/f
h. Continuing care	Subset of those engaged in treatment (g) that are still getting treatment after 90 days (whether via retention, transfer or booster)	h/g

**Table 5 Tab5:** Service cascade: crosswalk of quantitative and quality measures

	Example measures of quality		
Service cascade measure	Timing	Content indicators	Procedural indicators

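### H3 claims greater improvement from baseline, but the H3a test is worded as a difference in level between conditions, with no baseline or change term

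*Protocol article*

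**What the plan says.** Table 3 of the Protocol article (Hypotheses) states that, compared with Core, "the Enhanced intervention sites will have greater improvements (relative to baseline) during the experiment period in service quality in terms of" timing, content or procedure. A note to the table adds that "H3b & H3c are largely descriptive and exploratory", so H3a (timing) remains among the primary hypotheses.

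The analysis text under Hypotheses then reads "H3a utilizes bi-weekly intake cohorts and tests whether percentages of youth meeting" their timing targets "differ significantly between the 18 Enhanced and the 18 Core sites". The next remark on method is "Trends can be examined over time using simplified time series analysis".

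Two other places bear on the point. Study design describes sites as their own controls, "using an interrupted time series design with the baseline period as an existing practice control". The analysis paragraph for H1 and H2 tests H2, which has the same relative-to-baseline wording as H3, through a difference in slopes in a latent growth curve model.

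**The concern.** The hypothesis concerns the difference between conditions in how much sites improve. The test, as worded, concerns the difference between conditions in the percentage reached. In a realized sample of 36 sites these can disagree. A group of sites that was already fast and did not change could show a higher percentage, and a group that started slow and improved more could show none. A report that followed the analysis wording could present the first as greater improvement.

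The second cost is precision. Sites differ persistently in how quickly they screen, assess and refer. If the baseline is left out, that persistent variation stays in the error of a comparison based on 18 sites per arm.

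**Working it through.** **Text side by side.** H2 and H3 both claim greater improvement relative to baseline in Enhanced sites. H2 gets a slope contrast. The H4 analysis is described as focusing on change in staff responses. H3a gets a difference in percentages between two groups of sites. The time-series remark does not close the gap: it is permissive, and the article introduces simplified time series as a way to analyse data within sites, which gives no between-condition test of change.

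**The plan's own power figure.** The Power section gives 36 × 60 = 2160 bi-weekly observations, which reproduces. It claims at least 80 % power for effects of .25 to .35 at ICC .2 or less, but names no alpha or model. With a two-sided 5 % level (assumed) and ICC .2, the design effect is 1 + 59 × .2 = 12.8 and the effective n is 2160/12.8 = 168.8. Split over two arms, this gives a detectable effect of .431, outside the stated range. It falls inside (.305) only if 2160 is taken as the number per condition, or at a lower ICC (.317 at .1). The claim cannot be tied to one calculation, and the point here does not depend on it.

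**Precision of the H3a contrast.** Inputs:
- ICC r = .2 (the ceiling in Power), and .05 for comparison.
- 6 months of baseline and 12 of experiment (Measurement), taken as 13 and 26 bi-weekly periods.
- 18 sites per arm.
- Assumed: total variance 1, independent residuals within site, two-sided 5 %, 80 % power, and a correlation s of the site effect between periods.

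Formulas, per site:
- Experiment period only: Vp = r + (1 − r)/26
- Baseline mean: Vb = r + (1 − r)/13
- Baseline-adjusted: Va = Vp − (r·s)²/Vb
- Change score: Vd = Vp + Vb − 2·r·s
- SE of the contrast = √(2V/18); detectable effect ≈ 2.89 × SE (noncentral t, about 34 df)

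At r = .2, s = 1:
- Vp = .2 + .8/26 = .231; SE .160; detectable .46
- Vb = .2 + .8/13 = .2615
- Va = .231 − .04/.2615 = .078; SE .093; detectable .27; reduction 1 − .078/.231 = 66 %
- Vd = .231 + .2615 − .4 = .092; SE .101; detectable .29
- Power for an effect of .35: about 56 % experiment-only, 96 % adjusted

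At r = .2 with less stable site effects:
- s = .7: Va = .231 − .14²/.2615 = .156, a 32 % reduction; SE .132; detectable .38
- s = .5: Va = .231 − .10²/.2615 = .193, a 17 % reduction; SE .146; detectable .42

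At r = .05, s = 1:
- Vp = .05 + .95/26 = .0865; Vb = .05 + .95/13 = .1231
- Va = .0865 − .0025/.1231 = .0662, a 23 % reduction; detectable .28 to .25
- Vd = .0865 + .1231 − .1 = .1096, larger than Vp; detectable .32

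Baseline adjustment therefore gains in every case shown. A simple change score gains at ICC .2 with stable sites but loses at ICC .05.

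**The case against.** The article is condensed, and one loosely worded sentence need not mean that the baseline will be ignored. Bi-weekly cohorts are named, the design treats sites as their own controls, Core versus Enhanced is listed among the time-series comparisons, and H3a is nowhere confined to the experiment period. This stands as a limit on the claim: the experiment-only reading is one possible reading, and the precision figures apply only under it. It does not remove the mismatch, because the one sentence that states the test omits the element that defines the hypothesis, while the parallel sentence for H2 includes it.

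A reader might also infer that an unpaired, unadjusted test was chosen, since "one site in each pair was randomly assigned to Core and the other to Enhanced" and "The final randomization design was selected from a pool of the top 2 % of permutations balancing across all characteristics", yet no pair or balancing term appears for H3a. The documents do not support that. They are equally silent on pairs for H1, H2 and H4, such terms are commonly left to a fuller document, and Power mentions modeling site differences with covariates. Ignoring pairs would in any case be conservative. In simulation with 18 pairs, the type I error of the unpaired test is .049, .039, .021 and .007 at pair correlations 0, .1, .3 and .5. At zero correlation it is slightly more powerful than the paired test (83 % against 81 % for a 1-SD site difference).

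Nor can one say that chance baseline imbalance would be read as an effect. Condition was randomized under balance constraints, so the contrast is unbiased in expectation, and its standard error already allows for chance differences between sites.

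Finally, the 66 % figure is a favourable case: it uses the ceiling ICC and perfectly stable site effects. That is correct, and the range above should be quoted with it.

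**Conclusion.** The point holds as a mismatch between hypothesis and test for H3a, with a probable loss of precision. The mismatch rests on the text alone. The loss of precision rests on reading the test as experiment-period only, with 13 and 26 periods, 18 sites per arm and independent residuals. Under those assumptions, omitting the baseline forgoes a variance reduction of about 66 % at ICC .2 with stable site effects, 32 % or 17 % when site effects correlate .7 or .5 between periods, and 23 % at ICC .05 with stable effects. The between-period correlations are assumptions; the article gives none. No bias and no inflated type I error are shown, and nothing is established about how the matched pairs will be handled.

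**What to change.** Restate the H3a test as a comparison of experiment-period percentages between conditions, adjusted for the site's baseline percentage, with site as the cluster and site-level degrees of freedom. A condition-by-period contrast would also match the hypothesis. Baseline adjustment is preferable to a simple change score, which loses precision at low ICC. State that the simplified time series is supplementary. Pair or research-center terms are optional; 18 fixed pair effects would use 17 degrees of freedom.

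The cost is one degree of freedom for the baseline covariate (34 to 33 at site level) and a change of wording. The records needed are already being collected for the baseline period. The article reports uneven record quality across sites, so the rule for sites with poor baseline timing data should be fixed at the same time.

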**Fig. 3 Fig3:**
[figure not shown]
JJ-TRIALS Study Design

Primary research questions include:Does the Core and/or Enhanced intervention reduce unmet need by increasing Cascade retention related to screening, assessment, treatment initiation, engagement, and continuing care?Does the addition of the Enhanced intervention components further increase the percentage of youth retained in the Cascade relative to the Core components?Does the addition of the Enhanced intervention components improve service quality relative to Core sites?Do staff perceptions of the value of best practices increase over time, and are increases more pronounced in Enhanced sites?

The study also includes exploratory research questions. Examples include: How do sites progress through EPIS phases with and without facilitation? Are Enhanced sites more successful in implementing their chosen action plans, achieving greater improvement in cross-systems interagency collaboration, and experiencing greater reductions in 1-year recidivism rates? Is one condition more cost-effective than the other? And how do inner and outer context measures (e.g., system, organizational, staff) moderate relationships between experimental conditions and service outcomes?

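### Four of the seven H1/H2 Cascade rates are divided by steps the intervention is meant to change, so they can move against the share of youth actually reaching care

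*Protocol article*

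**What the plan says.** H1 and H2 (Table 3, under Hypotheses) name seven outcomes: the percentages screened, assessed, in need, referred, initiated, engaged and in continuing care. H2 predicts that "the Enhanced Intervention sites will have greater improvements (relative to baseline) during the experiment period in their percentage of" youth retained. The text after Table 3 repeats the growth-curve analysis for each outcome.

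Table 4 fixes the rates:

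- Screened, assessed and need identified are b/a, c/a and d/a, where (a) is all JJ referrals, net of youth already in treatment.
- Referred is e/d: "Subset of those in need (d), referred by the juvenile justice system to substance use treatment".
- Initiated is f/e: "Subset of those referred to treatment (e) who have treatment start date".
- Engaged is g/f: "Subset of those who initiate treatment (f) who stay in treatment for at least 6 weeks".
- Continuing care is h/g: "Subset of those engaged in treatment (g) that are still getting treatment after 90 days".

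The Hypotheses section is open about this. It describes the rates as "divided by the number in the earlier step, with dashed lines highlighting changes in the denominator" and justifies them as matching widely used performance metrics. The article defines no rate over (a) for steps e to h.

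The second primary research question, under Study design, asks whether Enhanced will "further increase the percentage of youth retained in the Cascade relative to the Core components". The abstract lists screening, assessment and linkage to treatment as target outcomes.

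**The concern.** The denominators d, e, f and g are counted after the intervention has begun to act, and the intervention is meant to change them. H1 and H2 themselves predict that the percentages in need and referred will rise. If a site identifies more youth, and the added youth are less likely to be referred, start or stay, then success upstream lowers the next rate, which the same hypothesis requires to rise.

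For H2, randomisation does not make the Enhanced and Core youth who reach d, e, f or g comparable. For H1 the comparison is a site with its own baseline, so the difficulty is a change in case mix between periods and not conditioning after randomisation.

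At stake is the answer to the trial's own question. A rate that leaves out youth who were never identified cannot show that gap closing. Read alone, it could report worse retention while more youth receive care, or better retention while fewer do.

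**Working it through.** The article states no expected Cascade rate, so there is no figure to reproduce. The check compares each step rate with the same step over all JJ referrals. All input rates below are assumptions.

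**Example A: two arms.** Take a = 1000 referrals per arm, of whom 200 severe and 200 marginal youth are in need. In both arms 80% of identified youth are referred, and initiation among those referred is 60% (severe) and 30% (marginal). Core identifies 70% of severe and 10% of marginal youth. Enhanced identifies 90% of severe youth and a varied share of marginal youth.

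Formulas: d = 200 × p(severe) + 200 × p(marginal); e = 0.8 × d; f = 0.8 × [200 × p(severe) × 0.6 + 200 × p(marginal) × 0.3].

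| Arm (severe / marginal identified) | d | e | f | f/e | f/a |
|---|---|---|---|---|---|
| Core (70% / 10%) | 160 | 128 | 72 | 56.3% | 7.2% |
| Enhanced (90% / 20%) | 220 | 176 | 96 | 54.5% | 9.6% |
| Enhanced (90% / 30%) | 240 | 192 | 100.8 | 52.5% | 10.1% |
| Enhanced (90% / 60%) | 300 | 240 | 115.2 | 48.0% | 11.5% |

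If both arms start from the same baseline rates, the last row gives an H2 contrast of 48.0 − 56.25 = −8.25 points on f/e and 11.52 − 7.2 = +4.32 points on f/a. The signs are opposite.

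Sensitivity to prognosis, in the 90% / 60% row:

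- Marginal youth initiate at 45%: Core f = 0.8 × (84 + 9) = 74.4 and f/e = 58.1%. Enhanced f = 0.8 × (108 + 54) = 129.6 and f/e = 54.0%.
- Marginal youth initiate at 60%, like the severe youth: f/e is 60% in both arms and there is no distortion.

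**Example B: one site before and after, on the article's minimum of 120 records.** Before: d = 30 and every later step at 60%, so e = 18, f = 10.8, g = 6.48 and h = 3.89. Then 18 more youth are identified (d/a from 25% to 40%) and referred at 60%. The 30 already identified keep the same outcomes. If the added youth pass each later step at 40%:

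- f = 10.8 + 18 × 0.6 × 0.4 = 15.12; f/e = 15.12 / 28.8 = 52.5% (was 60%); f/a = 12.6% (was 9.0%).
- g = 6.48 + 4.32 × 0.4 = 8.21; g/f = 54.3% (was 60%); g/a = 6.8% (was 5.4%).
- h = 3.89 + 1.73 × 0.4 = 4.58; h/g = 55.8% (was 60%); h/a = 3.8% (was 3.2%).

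With added-youth rates of 20%, 50%, 60% and 70%, f/e is 45.0%, 56.3%, 60.0% and 63.8%, while f/a is 10.8%, 13.5%, 14.4% and 15.3%. So f/e can fall, stay or rise, while f/a is above 9.0% every time.

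**Referral rate.** If referrals stay at 18 while d goes from 30 to 48, e/d falls from 60% to 18/48 = 37.5% with no youth worse off.

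**Reverse case.** If referrals are cut from 18 to 12 and 75% of those initiate, f/e rises from 60% to 75%. Treatment starts fall from 10.8 to 9, so f/a falls from 9.0% to 7.5%.

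**The case against.** The strongest reply has four parts.

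**The step rates are disclosed and useful.** They map onto outside performance systems, and sites choose which step to improve. A site working on engagement is measured directly by g/f, whereas g/a mixes in identification and referral. This stands, and it is why the step rates should stay and not be reduced to mere description. Nor is f/a a pure measure of unmet need, since its denominator includes youth without need.

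**The information is not lost.** The rates chain: f/a = d/a × e/d × f/e, or 0.30 × 0.80 × 0.48 = 0.115 in the 90% / 60% row. A reader who sees d/a rise from 16% to 30% can understand why f/e falls. This also stands, but the article specifies no test of the product, and each outcome is analysed separately.

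**The large example is generous.** Both arms receive every Core component, so 60% against 10% of marginal youth identified is a wide gap. At 20% the fall in f/e is only 1.7 points. The example also assumes no effect of Enhanced on initiation, although linkage is a target. A relative gain of about 17% (56.25 / 48 = 1.17) would cancel even the large fall. All of this is fair.

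**Stronger readings go too far.** A reader might infer that H2 as a whole is biased. The documents do not support that: three of its seven rates use all JJ referrals. For the other four, bias needs both a differential upstream change and a different prognosis in the added youth, and the article gives data on neither. A reader might also infer that row (a), "Total number of referrals to juvenile justice in time period with a disposition start date, less any youth already in treatment at that time", drops youth whose linkage was speeded up. That depends on one reading of an ambiguous time reference, and such youth would leave the denominator as well. The article gives no interval from which to size any loss, so the point is not made here.

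**Conclusion.** The concern holds in limited form. Four of the seven H1/H2 outcomes (e/d, f/e, g/f, h/g) condition on steps that the intervention is meant to change, and no outcome over all JJ referrals is specified for those steps. Their Enhanced-Core contrasts can compare differently selected youth, and their experiment-baseline contrasts can reflect a case-mix shift. b/a, c/a and d/a are free of the problem.

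Neither direction nor size can be fixed from the article. In the two-arm illustration the fall in f/e runs from 1.7 points (20% of marginal youth identified in Enhanced) to 8.25 points (60%), while f/a rises by 2.4 to 4.3 points. With equal prognosis the distortion is nil, with better prognosis in the added youth it reverses, and restricted referral can produce an apparent success. Every input rate is assumed. What does not rest on assumption is that these rates, taken one at a time, do not measure the percentage of youth retained that the research questions ask about.

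**What to change.** Add e/a, f/a, g/a and h/a, with all JJ referrals as the common denominator, as tested H1 and H2 outcomes. State that they carry the conclusion on the percentage of youth retained in the Cascade. Keep e/d, f/e, g/f and h/g beside them as step-specific process measures, and state that each is interpreted together with the upstream rates.

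No new data are needed: the same records supply every numerator and denominator. The costs are four more tested outcomes (eleven instead of seven) and smaller percentages. The cumulative rates are also less specific to the step a site has chosen to work on, which is the reason for keeping both sets.
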